## **9.3. Potential risks of research and what to do in the event of an adverse effect**

Given the category of research, RIPH2 Research with Minimal Risks and Constraints, the foreseeable risk added by the research is negligible (self-administered questionnaires), no serious adverse event linked to the acts and procedures of this research is predictable.

# **10. DATA COLLECTION AND PROCESSING**

The processing of the personal data of persons participating in this research has the sole purpose of carrying out the research. This processing includes the management of data relating to people taking part in research, with a view to enabling the collection, entry, checking of validity and consistency and statistical analysis of the data collected during the research.

As part of this research, two types of databases must be considered:

- (i) A research management base which will allow the practical carrying out of research in the field and which includes a certain number of nominative data. This base should mainly include the following variables: name of participating municipalities and randomization group; name of the middle schools, the principal/director, the nurse/doctor, the PrevHPV referent within each middle school; name of GPs and GPs participating in the training of each municipality; name and address of middle school students who have accepted vaccination on the middle school website (for sending the 6-month reminder, etc.). For monitoring within the framework of the KABP-6C survey more particularly,

The research management base will be accessible to the teams responsible for implementing the intervention in the field, that is to say teams 1, 2, 3, 5 and 7. It will be shared between these teams (computer network) and within each of the 5 teams, only authorized people have the right of access with identification of authorized users.

- (ii) A research database which contains all the data necessary to exploit the results corresponding to the research objectives, but no nominative data. The data collected will not identify the person who participated. Furthermore, there is no common variable allowing the link between the

research management base and the database. The accesses and the circuit of this data of this last base are described below. In the same way as for the management database, only authorized people have the right of access with identification of authorized users, in accordance with the operating procedures defined within the framework of the research.

The paragraphs below regarding the research database.

### ***10.1. Description of collected data***

The data collected to meet the objectives of this research are as follows. They were defined with a care for minimization:

- a) The main characteristics (number of middle schools, department, FDep, medical density) of the participating municipalities, as well as the participating middle schools (size of the middle school, REP(+) middle school or not, number of FTE school nurses/doctor, urban sector or rural).
- b) The main characteristics of GPs (age group, gender, seniority and area of practice, mode of practice, sector of practice).
- c) The data completing the SNDS data for the calculation of the vaccination coverage rate (1 dose, 2 doses) at the different times (before intervention, 2, 6 and 12 months after the end of the intervention) i.e., for each participating municipality, injection statistics in family planning and education centers and vaccination centers, as well as the number of vaccines administered in each middle school in groups 1 and 3 during the intervention.
- d) Data on individual characteristics, knowledge, attitudes, beliefs (opinions on the effectiveness, safety or usefulness of the vaccine), practices related to vaccination in general and HPV vaccination, antecedents of hesitancy vaccination, intention to vaccinate among adolescents, their parents, and GPs, and declared vaccination status.
- e) Data on health students' knowledge and vaccine hesitancy.
- f) Data on the satisfaction of the different target populations in relation to the actions implemented (SeSa students, middle school professionals, GPs/training, adolescents and parents/e-health tools made available).
- g) Data on the number of middle schools/municipalities asked to participate in the research and the number who accepted, the number and nature of the actions carried out for each of the 3 components, the participation of the target populations in the various actions carried out, possible adaptation of actions (compared to what was planned) according to the context and/or local constraints.
- h) Cost data: resources associated with each of the 3 components (design + implementation), collected from the project teams in charge of their development (for the tools), middle school referents, project managers and training centers. vaccination (for their implementation).

The data collected in b, d, e, and f are collected individually but anonymously, that is to say without collection of indirectly identifying variables.

Justification of the data collected:

| Data                                                                                                                                                                  | Rationale                                                                                                                                                                               |
|-----------------------------------------------------------------------------------------------------------------------------------------------------------------------|-----------------------------------------------------------------------------------------------------------------------------------------------------------------------------------------|
| Characteristics of municipalities and middle schools                                                                                                                  | Description of the municipalities / middle schools concerned by the 'EMM' and 'Facilitation of access' components of the intervention
Response to secondary objective 2              |
| Characteristics of GPs                                                                                                                                                | Description of the population concerned by the 'Training of GPs' component                                                                                                              |
| VC calculation data (in addition to SNDS data)                                                                                                                        | Estimation of the overall VC rate (Response to the primary objective)                                                                                                                   |
| Data on individual characteristics and knowledge, attitudes, beliefs, practices, history of vaccine hesitancy, intention to vaccinate and reported vaccination status | Evaluation of the impact of the different components in the different clusters using pre- and post-intervention questionnaires (Response to secondary objective 1)                      |
| Satisfaction data from different populations                                                                                                                          | Assessment of the satisfaction of different populations with the different components of the intervention and identification of levers and barriers (Response to secondary objective 5) |
| Implementation data                                                                                                                                                   | Evaluation at the individual and collective level of the implementation of the intervention and identification of levers and barriers (Response to secondary objective 5)               |
| Cost data                                                                                                                                                             | Evaluate the efficiency of the different components of the intervention and the cost of these different components alone and combined (Response to secondary objectives 3 and 4)        |

No individual health data, other than whether or not someone is vaccinated, is collected as part of this research.

Personal data (eligibility criteria and contact details) concern GPs in the 90 municipalities and participants in the KABP-6C survey.

Each participating municipality and middle school will be assigned a 'municipality code' and a 'school code' respectively. These codes will only be known by the PrevHPV SC project teams and will be linked in a file dedicated to a URL address allowing access to the questionnaires (KABP-6C questionnaire). At no time will the names and contact details of middle schools be recorded in a file containing the data collected from the populations studied. At no time will the names and contact details of participants in the KABP-6C survey be recorded in a file containing the data collected from participants.

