## 3. OUTCOMES

### 3.1. Primary outcome

To the primary objective correspond 1 primary outcome and 5 secondary outcomes (see first 2 lines of the table page 15) depending on the number of doses of vaccine administered (1 or 2 doses) and the time of measurement (2 months, 6 months or 12 months after the end of the intervention).

The primary outcome to assess the effectiveness of the different components of the intervention is the vaccination coverage rate (= prevalence of vaccination, i.e. at least 1 dose received) among adolescents aged 11-14 years, 2 months after the end of the intervention. This prevalence will be calculated overall, then separately for girls and boys.

Prevalence is defined as the number of adolescents aged 11 to 14 years who have received at least 1 dose of HPV vaccine (Cervarix®, Gardasil®, Gardasil9®) / the total number of adolescents aged 11 to 14 years. Prevalence before intervention implementation will be calculated among adolescents using the databases of the National Health Data System (SNDS, i.e. the national reimbursement database) (103), data from vaccination centers and family planning centers. We are aware that health insurance coverage for vaccination in boys starting in January 2021, pharmaceutical dispensation among

boys in the SNDS will most likely be close to 0. In the SNDS bases, we will count 14-year-olds who have received at least 1 dose in the last 4 years, 13-year-olds in the last 3 years, 12-year-olds in the last 2 years, and 11-year-olds in the past year.

The prevalence 2 months after the end of the intervention will be calculated using data from the SNDS, data from vaccination centers and family planning centers, and data from vaccination in middle schools. For the same dose of vaccine, it is therefore not possible for an individual to be present in several different data sources, and it is therefore not possible to count people twice. Indeed, if an adolescent (and their parents) decides to be vaccinated following the intervention, he or she has 4 possibilities of access to vaccination: be vaccinated by his or her attending physician (information available in the SNDS via the dispensation of the vaccine in a community pharmacy), get vaccinated in a vaccination center, get vaccinated in a family planning center, or get vaccinated at school as part of the PrevHPV intervention.

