| Evaluate the effectiveness of the intervention on the prevalence of vaccination (at least 1 dose received), 6 and 12 months after the end of the intervention (Primary Obj)     | Variation in the prevalence of vaccination (at least 1 dose) between before the start of the intervention and after the end (6 months and 12 months) among young people aged 11 to 14 years                     | Pre-intervention prevalence: number of young people aged 11 to 14 who have received at least one dose of vaccine (SNDS data, vaccination centers, planning centers) / the total number of young people in this age group.
Prevalence after the intervention: number of young people aged 11 to 14 who had received at least one dose of vaccine before the intervention + after the intervention (SNDS data + vaccination centers + planning centers + number of vaccines administered within middle schools) / the total number of young people in this age group.
Calculated globally and separately for boys and girls | Before the intervention
+ At 6 months and 12 months after the end of the intervention           |
| Evaluate the effectiveness of the intervention on the prevalence of complete vaccination (2 doses received), 2, 6 and 12 months after the end of the intervention (Primary Obj) | Variation in the prevalence of complete vaccination (2 doses received) between before the start of the intervention and after the end (2 months, 6 months and 12 months) among young people aged 11 to 15 years | Prevalence before the intervention: number of young people aged 11 to 14 who received two doses of vaccine (SNDS data, vaccination centers, planning centers) / total number of young people in this age group.
Prevalence after the intervention: number of young people aged 11 to 14 who had received two doses of vaccine before the intervention + after the intervention (SNDS data + vaccination centers + planning centers + number of vaccines administered within middle schools) / the total number of young people in this age group.
Calculated globally and separately for boys and girls                   | Before the intervention
+ At 2 months, 6 months and 12 months after the end of the intervention |

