- (ii) Planning two injections 6 months apart, preceded by the implementation of the EMM component, over a single school year was impossible since health students who participate in the EMM are only available beginning in January. In this context, carrying out the 2nd injection of the vaccine meant that some of the students (mainly those in Grade 9) had to be called back to the middle school even though they were no longer attending school there. This spread of the intervention over 2 school years raised numerous organizational difficulties.

However, measures will be implemented so that adolescents benefit from the complete vaccination schedule:

- mention of the 2nd injection to be carried out in both the written and oral information which will be provided by the doctor from the vaccination center (the date of the next injection will be mentioned orally and in post-vaccination letters) with provision of a prescription for the next injection,
- reminder letter as the 2nd injection approaches.

Once the list of the 30 municipalities benefiting from the 'Facilitation of access to vaccination' intervention has been identified (randomization in groups 1 and 3), contact is made with the DGESCO, the rectorate / diocesan management, the educational establishments, mayors, departmental councils and vaccination centers likely to intervene in educational establishments. A service contract is proposed between the University of Lorraine and the vaccination centers (with compensation for working time) so that they go to the middle schools of the different municipalities in question to vaccinate students whose parents consent to the vaccination.

The project managers of the PrevHPV team, in conjunction with each referent, are responsible for the practical organization of the “Facilitation of Access” intervention on site (date of the half-day(s) of vaccination, order and delivery of vaccines, etc.) and to create a link between middle schools and vaccination centers.

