## **8.1. Vaccine logistics circuit**

The purchase of vaccines administered as part of the PrevHPV - Facilitation of Access intervention (Gardasil9®, injectable suspension in pre-filled syringe Laboratoires MSD Vaccins) will be carried out in accordance with the procedures of the public procurement code, defined according to the overall cost of the vaccines. The purchase and supply of vaccines will be carried out and under the responsibility of one (or more) Pharmacy(ies) for In-house Use (PUI) of the participating regions, or failing that by a pharmaceutical service provider. For each middle school benefiting from the 'Facilitation of access' component, the middle school referent and the PrevHPV project manager of the region concerned will define the number of vaccines to be provided according to the feedback from vaccination consent forms. The vaccines will be sent to each vaccination center concerned a few days before the middle school vaccination day. On the day of the middle school vaccination, the mobile team from the vaccination center will transport the vaccines previously received. All vaccine deliveries (between the supplier and the PUI, between the PUI and the vaccination centers, between the vaccination centers and the middle schools) will respect the cold chain.

There will be no specific packaging and/or labeling of the vaccines as the vaccine itself is not the subject of the research. The present research aims to evaluate the effect on vaccination coverage of a change in access to vaccination, the vaccine in question having a marketing authorization for the population targeted by the study.

The entire drug circuit (purchase, supply to PUIs and vaccination centers, storage, transport to middle schools) will comply with current pharmaceutical regulations.

The preparation and organization of vaccination days is the subject of a procedure. The vaccine circuit is currently being developed.

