## 10.2. Source data and documents

Source data is all the information contained in original documents, or in authenticated copies of these documents, which relate to clinical examinations, observations or other activities carried out as part of research involving the person human and which are necessary for the reconstruction and evaluation of research. The documents in which the source data are recorded are called source documents, regardless of the medium used (paper, electronic, etc.).

The data a) are collected on a specially dedicated computer database and are shared by all the PrevHPV

SC teams. These data are public data, accessible via online statistics. They will be verified with the principals/directors of the middle schools.

Data b) are collected on a specially dedicated computer database and are shared between team 2 and team 3. They will be collected by teams 2 and 3 by interviewing the GPs participating in the training.

Data c): (i) SNDS data (for participating municipalities: reimbursement of a HPV vaccine for a young person aged 11 to 14, by sex, and prescribing health professional) will be made available to team 8 (dedicated data access portal) after contracting with the CNAM and obtaining authorizations. (ii) data from family planning and education centers, vaccination centers and number of vaccines used for research will be collected by teams 1, 3, 4, and 5 for each geographical area that each team is in charge of and will be transmitted to team 8 for the analysis of the main objective and to team 6 for the evaluation of efficiency.

Data d) are collected via the KAPB-6C self-questionnaires administered online to the different target populations on a database generated by team 7.

Data e) are collected via self-questionnaires administered online to SeSa students on a database generated by team 5.

Data f) on satisfaction with the interventions are collected via online or paper self-questionnaires. (SeSa students, middle school professionals, adolescents and parents will be managed by teams 4 and 5; GPs by team 2).

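### The plan says no dose can be counted twice, but vaccination-centre teams give the school doses and no rule keeps those doses out of the centres' own returns

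*Protocol*

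**What the plan says.** The primary outcome is coverage with at least one dose among 11-14 year olds, two months after the intervention ends. The section 3.2.1 table, which sets out the same measure at 6 and 12 months, gives the post-intervention numerator as a sum: "SNDS data + vaccination centers + planning centers + number of vaccines administered within middle schools". Section 3.1 names the same sources for the 2-month measure.

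The non-SNDS parts are aggregates per municipality. Section 10.1, item c), lists "injection statistics in family planning and education centers and vaccination centers, as well as the number of vaccines administered in each middle school" for groups 1 and 3. Section 10.2 repeats the two items and says who gathers them: "vaccination centers and number of vaccines used for research will be collected by teams 1, 3, 4, and 5".

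On double counting, section 3.1 states: "For the same dose of vaccine, it is therefore not possible for an individual to be present in several different data sources". Its reason is that an adolescent has four ways to be vaccinated: through the physician, at a vaccination centre, at a family planning centre, or at school within PrevHPV.

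Section 8 describes how the school route works. Vaccination centres are offered a service contract "so that they go to the middle schools of the different municipalities in question to vaccinate students whose parents consent to the vaccination". The centre's doctor vaccinates and its nurse assists. Section 8.1 adds: "The vaccines will be sent to each vaccination center concerned a few days before the middle school vaccination day".

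**The concern.** The section 3.1 argument concerns where a person goes. The numerator depends on who reports the dose. School is a separate place from the centre, but it is not a separate operator: the centre supplies the staff and holds the vaccine for the school day. A centre asked for its injection statistics could include those sessions or leave them out, and nothing in sections 3.1, 8, 10.1 or 10.2 tells it which to do. The issue is one injection appearing in two returns, not a later second dose for the same adolescent.

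School doses exist only in groups 1 and 3. Any overlap therefore falls on the arms with Facilitation, always raises their coverage, and cannot cancel against the other arms. The same sum feeds the 6- and 12-month outcomes, and the 2-month coverage feeds the cost-effectiveness ratio.

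De-duplication by person is not available as a later remedy. Section 10 says "there is no common variable allowing the link between the" management base, which holds the names, and the research database.

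**Working it through.** **1. The plan's own figure, to fix the scale.** Inputs from section 11.2: 16.1% initiation in girls, 0% in boys, girls 48.85% of the age group, mean cluster size m = 466, coefficient of variation 0.5, ICC 0.05, 90% power, alpha 5% (two-sided, section 11.3.1).

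- Baseline: 0.161 × 0.4885 = 7.86%.
- Individuals per arm for 7.86% v 17.86%: 234.
- Design effect: 1 + ((0.5² + 1) × 466 − 1) × 0.05 = 30.075.
- Clusters per group: 234 × 30.075 / 466 = 15.1. Power at 15 clusters is 89.9%.
- Total: 90 × 466 = 41,940.

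The stated 15 clusters per group reproduce, and only if the target is read as 10 percentage points. Read as a relative 10% increase, the design would need about 1,662 clusters per group. Ten points is therefore the yardstick below.

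**2. Size of a double count.** Let s be the share of 11-14 year olds vaccinated at school, and f the share of those doses that also appear in a centre's return. True coverage counts each dose once, while the sum counts a share f of the school doses again. Excess coverage in groups 1 and 3 is s × f; in the other four groups it is 0. The protocol gives neither s nor f, so the values below are assumptions.

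| s | f = 0.25 | f = 0.5 | f = 1 |
|---|---|---|---|
| 2% | 0.5 points | 1.0 | 2.0 |
| 5% | 1.25 | 2.5 | 5.0 |
| 10% | 2.5 | 5.0 | 10.0 |

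The range is 5% to 100% of the 10-point target. In doses, a 5-point excess is 466 × 0.05 = 23.3 per municipality, or about 699 over the 30 municipalities of groups 1 and 3. If no centre return includes a school session (f = 0), the excess is 0.

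**3. What an excess could do to the test.** Given EMM, the Facilitation contrast is groups 1 and 3 against groups 2 and 4: 30 v 30 clusters. Effective size per side is 30 × 466 / 30.075 = 464.8. The calculation assumes that school doses only replace other routes, so there is no true gain, and it ignores adjustment for baseline coverage.

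- Excess 3 points: SE = √[(0.0786 × 0.9214 + 0.1086 × 0.8914) / 464.8] = 1.91 points. The test rejects about 34% of the time.
- Excess 5 points: SE = √[(0.0786 × 0.9214 + 0.1286 × 0.8714) / 464.8] = 1.99 points. The test rejects about 69% of the time.

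Both use a two-sided 5% t-test on 56 degrees of freedom. They show how sensitive the test is and do not estimate the risk in this trial.

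**The case against.** The strongest reply is that the text can be read by place. Section 3.1 sets vaccination in a centre against vaccination at school, and section 10.1 asks for injections in centres and, separately, doses in schools. On that reading the categories do not overlap and the intent is clear. This stands as a statement of intent. It does not stand as a rule, because the term is nowhere defined for the centres that must fill in the return.

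Second, the means of separating the counts exist. Under section 8 each injection is marked on a list and the number of vaccinations carried out is part of the day's assessment. The same field teams gather both counts, and subtracting aggregates needs no names. This is correct and is why the fix is cheap, but no passage says that the subtraction is made.

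Third, section 11.3.1 plans a sensitivity analysis on SNDS data and school doses alone, which is free of this overlap. It is, however, conditional on the quality of what centres report, and it is not the primary analysis. A complete and accurate return that happens to include school sessions would not look like poor data.

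Fourth, the details of a return might be left to the data management and analysis plan announced in section 11.3. That is fair for the mechanics. It does not cover section 3.1, which already declares double counting impossible on a ground that section 8 does not support.

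A reader might also infer that centres ordinarily count off-site work, so that doses will in fact be counted twice. The documents do not say how centres report, so this cannot be claimed. Nor is collection by the delivering teams part of this point: it is a separate matter, and moving collection to another team is not needed to prevent the overlap.

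**Conclusion.** The point holds as a gap between an asserted property and the procedure meant to deliver it. The primary numerator sums two counts that share one operator, no exclusion is stated, and the assurance in section 3.1 does not close the gap. If centre returns include PrevHPV school sessions, coverage in groups 1 and 3, and hence the Facilitation effect, is overstated by s × f: 0.5 to 10 points over the assumed ranges, and zero if the sessions are left out.

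It would go too far to read the upper end, or the 34% and 69% rejection rates, as the expected error. The 10-point figure needs 10% school uptake and every school dose repeated in a centre return. The rejection rates also need no net gain from school vaccination. No figure in the protocol supports or excludes these values. The action rests on the direction and location of the possible error, which is always upward and only in the Facilitation arms of the primary outcome, and on how little it costs to rule out.

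**What to change.** In sections 10.1 c) and 10.2, state that vaccination-centre injection statistics exclude injections given in PrevHPV school sessions. Before the counts are summed, reconcile each centre's return, municipality by municipality, with the number of vaccinations recorded on the school vaccination days under section 8. In section 3.1, keep the no-double-count statement but rest it on this exclusion rule in place of the access routes.

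The cost is one line on the data request and one reconciliation check. It should be settled before the returns are requested, because an aggregate that mixes the two kinds of session may not be separable afterwards. No sample-size figure changes.
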